# Impact of effectiveness information format on patient choice of therapy and satisfaction with decisions about chronic disease medication: the "Influence of intervention Methodologies on Patient Choice of Therapy (IMPACT)" cluster-randomised trial in general practice

**DOI:** 10.1186/1472-6963-13-76

**Published:** 2013-02-25

**Keywords:** RCT, Shared decision making, Risk communication, Prognosis, Absolute risk reduction, Prolongation of life, Cardiovascular disease, Primary prevention, Health behaviour, General practice

## Abstract

**Background:**

Risk communication is an integral part of shared decision-making in health care. In the context of interventions for chronic diseases it represents a particular challenge for all health practitioners. By using two different quantitative formats to communicate risk level and effectiveness of a cholesterol-lowering drug, we posed the research question: how does the format of risk information influence patients’ decisions concerning therapy, patients’ satisfaction with the communication as well as confidence in the decision. We hypothesise that patients are less prone to accept therapy when the benefits of long-term intervention are presented in terms of prolongation of life (POL) in months compared to the absolute risk reduction (ARR). We hypothesise that patients presented with POL will be more satisfied with the communication and confident in their decision, suggesting understanding of the time-related term.

**Methods/Design:**

In 2009 a sample of 328 general practitioners (GPs) in the Region of Southern Denmark was invited to participate in a primary care-based clinical trial among patients making real-life clinical decisions together with their GP. Interested GPs were cluster-randomised to inform patients about cardiovascular disease (CVD) risk and the effectiveness of statin therapy using either POL or ARR. The GPs attended a training session before informing their patients. Before training and after the trial period they received a questionnaire about their attitudes to risk communication and the use of numerical information. Patients’ redemptions of statin prescriptions will be registered in a regional prescription database to evaluate a possible association between redemption rates and effectiveness format. The Combined Outcome Measure for Risk Communication And Treatment Decision Making Effectiveness (COMRADE) questionnaire will be used to measure patients’ confidence and satisfaction with the risk communication immediately after the conversation with their GPs.

**Discussion:**

This randomised clinical trial compares the impact of two effectiveness formats on real-life risk communication between patients and GPs, including affective patient outcomes and actual choices about acceptance of therapy. Though we found difficulties in recruiting GPs, according to the study protocol we have succeeded in engaging sufficient GPs for the trial, enabling us to perform the planned analyses.

**Trial registration:**

ClinicalTrials.gov Protocol Registration System
http://ww.clinicaltrials.gov/NCT01414751

## Background

In a time when shared decision-making is widely recommended for clinical practice, risk communication – an integral component of shared decision-making – has become an important factor in the doctor-patient encounter
[1-4]. This is especially true for patients confronted with the risk of a possible future chronic disease such as cardiovascular disease. Here the decision concerns lifestyle changes or initiation of long-term preventive medication to reduce the risk of adverse outcomes. Pharmaceutical interventions offer well-documented benefits at the population level. To the individual patient, however, the immediate clinical effect may be side-effects, whereas benefits may not be possible to identify or measure directly. For shared decision-making to be achieved risk communication is crucial. Effective risk communication can enhance knowledge, involvement in decisions about interventions, autonomy and empowerment of patients
[5]. In contrast, poor communication can lead to anxiety, lack of confidence in the doctor, and to decisions based on misinterpreted information and inadequate communication.

Communicating risk requires skills not always mastered by patients or doctors alike
[6-11]. Skill acquisition is of particular importance when the different numerical presentations of risk are communicated between doctors and their patients. The standard quantitative effectiveness formats are

•RRR - relative risk reduction

•ARR - absolute risk reduction

•NNT - number needed to treat

•POL – prolongation of life (or disease-/symptom-free survival) (Table 
1).

**Table 1 T1:** Four different ways of expressing the effect of preventive cholesterol-lowering therapy to a hypercholesterolaemic person

**Format**	**Examples of ways of expression**
RRR	If a person with high cholesterol level like you takes the medicine, the risk of dying from a heart attack will be reduced by 33% within the next 10 years
ARR	If people with high cholesterol level like you do not take the medicine on average 15 out of 100 people, 15%, will die of a heart attack within the next 10 years. However, if people take the medicine on average 10 out of 100, 10%, will die of a heart attack over the next 10 years. That means that on average 5% fewer persons will die
NNT	If 20 people with high cholesterol level like you take the medicine, there will on average be one more alive after 10 years than if they do not take the medicine
POL	If people with high cholesterol level like you take the medicine, for the rest of their lives they will on average live 8 months longer than if they do not take medicine

Several studies have evaluated these formats in risk communication and how they can be used in the doctor-patient encounter
[12-16]. The choice of format depends on various factors, e.g. whether the format is perceived to be easy to understand; whether it is correctly understood; whether the format meets patients’ information needs; whether patients receive enough information to make optimal decisions
[17,18]; and how understanding of the format may be affected by factors like age, gender, or educational level. By presenting risk in different ways, framing effects may influence how it is perceived
[19]. A body of research demonstrates that even when conveying essentially the same information, patients, doctors and policy-makers are influenced by differences in format, including the specific wording and presentation (e.g. percentages versus natural frequencies)
[15,20]. Pictorial representations seem to be better understood than natural frequencies, and natural frequencies better than percentages
[15]. A Danish study
[13] has indicated that respondents in a survey tend to be more consistent in their decisions when information is presented in terms of ARR rather than RRR or NNT. Absolute risk is often used by GPs when they communicate risk with their patients and discuss cardiovascular prevention. The GPs often make use of the Systematic Coronary Risk Assessment chart (SCORE)
[21] or national modified algorithms
[22-26]. The SCORE algorithm calculates a person’s 10-year statistical risk of fatal cardiovascular disease by means of the absolute risk in percentages, based on the patient’s gender, age, smoking status, systolic blood pressure and total-cholesterol.

The use of POL in effectiveness communication is a relatively new format of risk reduction. A study of osteoporosis interventions
[27] found that lay people seem to understand POL in the sense that they were able to discriminate between different levels of effectiveness when presented in terms of disease-free survival (i.e. “postponement” of hip fracture), but not in terms of NNT. Similar results have been shown in later studies
[14,28,29]. The studies indicate that the formats representing the most comprehensible effectiveness may be ARR and POL. A recent Danish study
[30] proposes a modified algorithm which is based on the same stratifications as the SCORE model. It presents the estimated ten-year mortality risk without statin treatment and the estimated ARR in percentages with treatment, and with inclusion of non-CVD mortality to provide estimates of all-cause mortality. Further, the modified algorithm provides estimates of the remaining life expectancy without treatment and the POL in months if treated with a statin. Providing risk and extension estimates with and without treatment makes it possible to inform patients about the expected gain on offer. The modified algorithm (see Additional file
1) forms the basis of the intervention in the IMPACT trial described in this study protocol.

Many studies on risk communication explore the conceptual development as to comprehension and presentation of risk
[31] or how lay people, doctors or policy makers choose treatment in hypothetical situations. Studies have involved patients
[6], but rarely for decisions about their own therapy. It is therefore unclear how closely the findings in hypothetical situations accord with real-life decisions. To the best of our knowledge, no randomised practice-based studies have yet explored how real patients’ real-life decisions are influenced by different risk formats.

## Objective and hypotheses

The primary objective of the IMPACT trial was in a randomised design to explore how risk communication using ARR versus POL as effectiveness format may affect a range of endpoints: patients’ decision about redemption of statin prescriptions, patients’ satisfaction with the communication in the consultation and patients’ confidence in their decision. Secondarily, we aimed to study the impact of teaching the GPs to use the respective effectiveness formats on GPs’ opinions and experiences in relation to statin prescribing and risk communication. We chose to use cholesterol-lowering therapy with statins, as hypercholesterolaemia is a well-defined condition, and because statins as the predominant treatment of hypercholesterolaemia are used for this condition only, ensuring that prescribed treatment is used for CVD prevention.

Based on previous research
[13,14,27,32] we hypothesise that patients understand POL better than ARR because most people have more experience with assessment of differences in time than reduced percentages in risk.

## Methods

### Design and setting

This cluster-randomised practice-based study has been implemented among GPs (single-handed or partnership practices) in the Region of Southern Denmark and their candidate patients for primary CVD prevention with statins.

### Randomisation

Randomisation took place at the level of general practices and allocated the practices to one of two different ways of presenting the effectiveness of cholesterol-lowering therapy. At an afternoon meeting with several practices gathered, randomisation was based on grouping of doctors in pairs using geographical location as first criterion, then type of practice (single-handed or partnership). In each pair one GP was allocated to ARR, and the other to POL based on a random-number computer-generated table prepared before recruitment of general practices.

When visiting individual single-handed practices during working hours a concealed random-number computer-generated table with block randomisation of the two formats in groups of 4 was used for allocation, and an alternative list used for partnership practices.

### Participants

#### GPs

In August 2009 the Regional Council of Southern Denmark, provided us with a list of 328 GPs in 13 municipalities in the Region of Southern Denmark (1.2 million inhabitants). At first we had planned to invite only GPs from two of the municipalities, Kolding and Fredericia (a total of 93 GPs), to obtain the number of practices needed. However, we did not succeed in recruiting enough GPs, and in October 2009 we consequently decided to invite all GPs on the list. We invited GPs to participate in a clinical trial concerning use of quantitative effectiveness formats in risk communication in health prevention consultations (typical consultations at which a GP would review risk factors, levels of risk and potential benefits of lifestyle or pharmacological interventions to manage risk). Subsequently, the project manager ([name]) contacted the GPs by phone and provided further details about the trial. During this phone call, the GPs were briefly informed about practicalities if they accepted to participate.

A total of 30 practices (18 single-handed and 12 partnership practices) were included in the study (Figure 
1).

**Figure 1 F1:**
[figure not shown]
Flowchart of GP enrolment.

#### Patients

The GPs have been asked to invite patients to participate in the trial if the patients have had blood samples taken for measurement of total-cholesterol and subsequently returning for a health prevention consultation. Patients aged 40 to 69 years with a total-cholesterol level above 4 mmol/L (155 mg/dL) will be eligible. This level is in accordance with Danish national guidelines for prevention of ischaemic CVD
[25]. Patients will be excluded if they have diabetes, known CVD (including stroke, angina or myocardial infarction), if they have already received cholesterol-lowering medication, or if they are not fluent in Danish. The patients will be informed verbally that the trial concerns the way GPs communicate risk with their patients and the patient’s perception of the risk communication.

The patients will receive a written description of the project including a letter of consent to be signed by the patient before entering the trial. The GPs will fill out a specially designed form with information on the individual patient’s age, gender, systolic blood pressure, total-cholesterol, and whether the patient consents to participate.

[40-42] the instrument has been forward-translated from English into Danish and back-translated into English, and finally tested for content validity. The remaining items of the questionnaire concern sociodemographic issues (education, household income, marital status), experience with cardiovascular disease in the patient’s family and self-rated health. Ideally, the questionnaire is to be answered immediately after the consultation for the patients to have a clear memory of the consultation. The patients are to return the questionnaire in a prepaid envelope addressed to the research group. Patients who do not return the questionnaire will receive up to two postal reminders.

After patient recruitment has ended, we will ask the GPs to complete a second questionnaire concerning their experiences with using the agreed quantitative effectiveness format they have been allocated when discussing preventive therapies with their patients.

### Outcomes

The primary outcome measure is patients’ redemptions of statin prescriptions based on data from Odense University Pharmaco-Epidemiological Database (OPED) during a three-month period after inclusion (the day the patient receives risk information and consents to participate). The three months will allow for time to consider and adopt lifestyle changes before initiating cholesterol-lowering therapy in accordance with Danish guidelines for primary prevention of CVD
[22].

OPED covers all individuals in the Region of Southern Denmark and captures information on redemption of reimbursed drugs. Based on the Anatomical Therapeutic Chemical (ATC) classification
[43], OPED has information on the number of packages and number of Defined Daily Doses (DDDs) dispensed, prescriber identification, and date of prescription.

The secondary endpoints are patients’ understanding of the provided risk information, their perception of involvement, confidence in the decision made, and satisfaction with the communication. Here, we will use the COMRADE instrument
[33-39].

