### Sample size

We based the sample size calculation on expected redemptions of statin prescriptions in the two groups. We expected 80% redemption in the ARR group and 60% in the POL group. This would require 2 groups of each 91 patients to obtain an 80% power with 5% significance in a non-clustered study. Due to clustering, and assuming an intra-cluster correlation of 0.1, we estimated a need for a total of 346 patients for 80% power and 5% significance. We included some buffer due to possible drop-outs and ended up with a total of 380 patients expected to be included by a total of 40 practices.

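### The three-month redemption window coincides with the time allowed for lifestyle change before a statin, so deferred starts may be counted with non-acceptance

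*Protocol article*

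**What the plan says.** The Outcomes section of the protocol article defines the primary outcome as redemption of statin prescriptions recorded in the regional database (OPED) "during a three-month period after inclusion (the day the patient receives risk information and consents to participate"). The next sentence gives the reason for the length: "The three months will allow for time to consider and adopt lifestyle changes before initiating cholesterol-lowering therapy", with a reference to Danish guidelines.

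Elsewhere the article uses redemption as the measure of a choice. The abstract's hypothesis is that "patients are less prone to accept therapy when the benefits of long-term intervention are presented in terms of prolongation of life (POL") than as ARR, and its discussion describes the trial as "including affective patient outcomes and actual choices about acceptance of therapy". The Background section treats lifestyle change as one branch of the same decision: "Here the decision concerns lifestyle changes or initiation of long-term preventive medication".

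The Sample size section states: "We expected 80% redemption in the ARR group and 60% in the POL group". It does not say over what period those rates apply.

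The article describes no second window, time-to-redemption analysis or category for deferred decisions. According to the Outcomes section, OPED covers everyone in the region and holds prescription dates.

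**The concern.** The window opens on the consultation day and closes three months later. The reason given for that length is that patients may want to try something else before starting a statin. A patient who does so for most or all of the period, and then starts, may have a first redemption just beyond the cut-off. The outcome then places that patient with those who did not accept therapy, although the patient did accept, only later.

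The effect on the comparison depends on whether such delay is the same in both arms:

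- **Equal delay** lowers both observed rates and narrows the difference between them.
- **Unequal delay** can create, hide or enlarge a difference that has nothing to do with acceptance.

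Unequal delay matters more here. The trial asks whether the format of the information changes the decision, and lifestyle change is part of that decision. One format could plausibly lead more patients to try lifestyle change first.

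**Working it through.** **Step 1. Timing.** Both periods come from the Outcomes section.

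| | Starts | Length |
|---|---|---|
| Redemption window | day of risk information and consent | three months |
| Time allowed for lifestyle change before a statin | same window | the same three months |

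The text does not say that lifestyle change must fill the whole period. The overlap shows that late starters can be missed; it does not show how many.

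**Step 2. The plan's own sample size.** Inputs from the Sample size section: 80% versus 60%, 80% power, 5% significance (taken as two-sided), intra-cluster correlation 0.1. The plan states "2 groups of each 91 patients to obtain an 80% power with 5% significance in a non-clustered study" and, "assuming an intra-cluster correlation of 0.1, we estimated a need for a total of 346 patients for 80% power and 5% significance".

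- Uncorrected: n′ = [1.96·√(2·0.7·0.3) + 0.8416·√(0.8·0.2 + 0.6·0.4)]² / 0.2² = (1.270 + 0.532)² / 0.04 ≈ 81.2, so 82 per group.
- Continuity-corrected: n = (n′/4)·[1 + √(1 + 4/(n′·0.2))]² ≈ 90.9, so 91 per group. This matches.
- Design effect with 10 patients per cluster (my assumption): 1 + 9·0.1 = 1.9. Then 182·1.9 = 345.8, so 346. This matches. With 380/40 = 9.5 per practice the total would be 337.

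The sample-size arithmetic is not in question.

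**Step 3. Delay that differs by arm.** Observed rate = eventual acceptance × (1 − share starting after month three). All shares are assumptions.

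| Eventual ARR / POL | Late in ARR | Late in POL | Observed ARR / POL |
|---|---|---|---|
| 80% / 80% | 0 | 25% | 80% / 60% |
| 80% / 60% | 25% | 0 | 60% / 60% |
| 80% / 60% | 0 | 25% | 80% / 45% |

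In the first row there is no difference in acceptance, yet the observed contrast is exactly the one the trial was sized to detect (0.80·0.75 = 0.60). In the second row a real difference disappears; in the third it is enlarged.

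**Step 4. Equal delay, only if 80% and 60% are eventual rates.** Let f be the share of accepters in both arms who start after month three. Power is at the planned information (91 effective patients per arm, continuity-corrected), which leaves the shortfall in practices out of the calculation. The last column is the total needed for 80% power at design effect 1.9.

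| f | Observed rates | Difference | Power | Total needed |
|---|---|---|---|---|
| 0 | 80% / 60% | 20 points | 80% | 346 |
| 10% | 72% / 54% | 18 points | 66% | 468 |
| 20% | 64% / 48% | 16 points | 53% | 620 |
| 25% | 60% / 45% | 15 points | 47% | 707 |
| 30% | 56% / 42% | 14 points | 41% | 814 |
| 50% | 40% / 30% | 10 points | 24% | 1429 |

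Worked example, f = 25%: removing the continuity correction gives n′ = 91·[1 − 1/(91·0.15)]² ≈ 78.2. Then z = [0.15·√78.2 − 1.96·√(2·0.525·0.475)] / √(0.60·0.40 + 0.45·0.55) = (1.326 − 1.384)/0.698 ≈ −0.083, which is a power of 47%.

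If 80% and 60% are rates within three months, only the row f = 0 applies and no power is lost.

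**The case against.** The strongest reply is that three months was chosen to be long enough for reflection, some lifestyle change and a first redemption. The wording permits this reading. It allows for delay and does not equate the window with the delay. The guideline it cites is not available here, so the expected length of a lifestyle phase cannot be checked. This stands, and it is why the number affected must be left as unknown.

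A reader might infer four stronger points that the document does not support.

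- **That late starters are counted as refusers.** The article measures redemption and never classes non-redeemers as having refused. The difficulty arises when non-redemption is interpreted as not accepting therapy.
- **That the trial loses power by a known amount.** The sample size was based on expected redemptions, and redemption is defined over three months. The 80% and 60% may therefore already be rates within the window, and reducing them again would count delay twice.
- **That the primary window is wrong and must be replaced.** A longer window captures deferred starts but also starts less related to the consultation. Neither length is clearly superior as the primary one.
- **That failing to separate a declined statin from one never offered is a further flaw.** The section on strengths and limitations already says that little will be known about the content of consultations. In a practice-randomised trial, the GP's prescribing response is arguably part of the effect under study.

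It could also be said that a longer-window analysis belongs in a full protocol or analysis plan, so its absence from an article is no fault. That is fair as to the absence. The point here rests on what the article does fix: a primary window, together with a rationale that draws attention to starts near or after its end.

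**Conclusion.** The concern holds in a limited form. The redemption window and the time allowed for lifestyle change are the same three months, so some patients who accept therapy after trying lifestyle change may be counted with those who did not accept. If the format influences who does this, the three-month contrast mixes timing with acceptance, and the bias can run in either direction.

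The size cannot be determined from the document. Under assumed late-start shares of 10% to 50% in both arms, and only if 80% and 60% are eventual rates, power at the planned size would fall from 80% to between 66% and 24%. If those rates already refer to three months, there is no loss. The interpretive problem does not depend on that choice: a quarter of POL accepters starting late would be enough to produce 80% versus 60% from equal eventual acceptance of 80%.

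The three-month result remains valid as a comparison of redemption within three months.

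**What to change.** Before any OPED linkage:

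1. Keep the three-month outcome as primary and prespecify a second analysis by arm, using the same model: first statin redemption within six months of inclusion, or time to first redemption over six months.
2. Take both results from the same OPED extraction and report them side by side.
3. State in advance that the three-month conclusion is limited to redemption within three months unless the six-month result agrees.
4. State whether the 80% and 60% planning rates refer to the three-month window.

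The cost is an extraction three months later and one extra analysis, with no patient contact. The price in interpretation is that starts in months four to six may be less related to the consultation, which is why the longer window is proposed beside the primary analysis and not in its place. Nothing here bears on when therapy should start.
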